## Abstract

**Background:**

For patients on HIV treatment in sub-Saharan Africa, the highest risk for loss from care remains the first six months after antiretroviral (ART) initiation, when patients are not yet eligible for differentiated service delivery (DSD) models that offer lower-burden, patient-centred care and thus improve treatment outcomes. To reduce early disengagement from care, the PREFER study will use a sequential mixed-methods approach to describe the characteristics, needs, concerns, and preferences of patients in South Africa and Zambia 0-6 months after ART initiation or re-initiation.

**Protocol:**

PREFER is an observational, prospective cohort study of adults on ART for ≤6 months at 12 public healthcare facilities in Zambia and 18 in South Africa. Its objective is to describe and understand the needs and preferences of initiating and re-initiating ART clients to inform the design of DSD models for the early HIV treatment period, improve early treatment outcomes, and distinguish the barriers encountered by naïve patients from those facing re-initiators. It has four components: 1) survey of clients 0-6 months after ART initiation (identify characteristics and preferences of clients starting ART); 2) follow up through routinely collected medical records for <24 months after enrollment (describe resource utilization and patterns and predictors of engagement in care); 3) focus group discussions and discrete choice experiment (explore reported barriers to and facilitators of retention); and 4) in South Africa only, collection of blood samples (assess the prevalence of ARV metabolites indicating prior ART use).

**Conclusions:**

PREFER aims to understand why the early treatment period is so challenging and how service delivery can be amended to address the obstacles that lead to early disengagement from care. It will generate information about client characteristics and preferences to help respond to patients’ needs and design better strategies for service delivery and improve resource allocation going forward.

## Introduction

Rapid, same-day, and community-based initiation of antiretroviral therapy (ART) for HIV has shifted the challenge of achieving optimal outcomes in HIV treatment onto retention in care after a patient has started ART. The highest risk for loss from care consistently remains a patient’s first six months after ART initiation
^
1
^. Dubbed the “early retention” period
^
2
^, this interval accounts for roughly three quarters of all first-year attrition from HIV programs in sub-Saharan Africa
^
3
^. In South Africa, 26% of patients were lost to follow up by 6 months after initiation in a recent trial of a case management intervention
^
4
^, and attrition was 35.6% by 6 months in a recent observational study
^
5
^.

Patient characteristics and service delivery characteristics both contribute to high attrition during the early treatment period
^
1
^. After the World Health Organization (WHO) began recommending universal treatment access in 2016, the median CD4 count of new ART initiates rose substantially, reflecting the much higher proportion of asymptomatic, “healthy” patients than in the past
^
6
^, despite a fairly consistent minority of a quarter to a third continuing to present with very low CD4 counts
^
7,
8
^. The proportion of patients who are re-initiating ART after previously interrupting care is also climbing. A recent modeling exercise estimated that in 2020, fully 58% of those who tested positive for HIV were already aware of their positive status
^
9
^ and thus may have declined an earlier opportunity to start or remain on treatment. Two small studies in South Africa identified ARV metabolites—evidence of recent exposure to ARV medications—in 53% and 19% of self-reported naïve ART initiators in Limpopo and KZN provinces, respectively
^
10,
11
^. Individuals who know their HIV-positive status but are not on ART likely face multiple barriers to starting treatment; those who both know their status and have already started and stopped ART at least once (re-initiators) may require additional support to remain in care once they re-initiate care.

The service delivery landscape has transformed at many points in the HIV treatment cascade in recent years, most notably through the introduction of rapid and same-day ART initiation for those not yet on treatment
^
12
^ and the development of patient-centred differentiated service delivery (DSD) models for those already established on ART for at least 6 months
^
13
^. Neither same-day initiation nor most current DSD models, however, offer solutions for patients during the first six months after initiation
^
14
^. The model of care for the early treatment period that is offered to most newly-initiating and re-initiating patients has evolved little from its original outlines, though COVID-19 restrictions precipitated some reductions in required numbers of clinic visits and increases in dispensing intervals
^
15
^.

A first step in designing new models of care for the early treatment period is to gain a comprehensive understanding of patients’ needs, concerns, resources, and preferences for service delivery during this period. Treatment and retention in the first 6 months after ART initiation could be improved if patients were triaged to receive more or less support based on a combination of known risks to retention in care and patient preferences for how little or how much interaction, and what kinds of interaction, with the health system are desired.

In the PREFER study, we will use a sequential mixed-methods approach to survey a sample of patients in South Africa and Zambia at various points between months 0 and 6 after ART initiation to develop a detailed profile of different groups of patients who may be best served by different models of care. The specific objectives of the study include describing the characteristics and preferences of new and re-initiating ART clients, exploring their concerns in depth through focus groups, identifying associations between client characteristics and early treatment outcomes, and assessing differences between naïve and non-naïve treatment initiators.

## Protocol

### Overview

PREFER is an observational, prospective cohort study in South Africa and Zambia that aims to inform the design of service delivery models for the early HIV treatment period. Its primary objective is to describe and understand the needs of initiating and re-initiating ART clients in order to inform the design of DSD models for the early HIV treatment period and improve early treatment outcomes. It has four components: 1) a survey of clients during the period from 0 to 6 months after ART initiation; 2) follow up through routinely collected medical records for a maximum of 12 or 24 months after study enrollment, depending on the study country; 3) focus group discussions (FGDs) and a discrete choice experiment (DCE) to explore specific issues raised in the survey; and 4) in South Africa only, collection of blood samples from a subsample of who self-report that they are not currently on ART and are initiating ART on the day of study enrollment to assess the prevalence of ARV metabolites indicating prior ART use (
Figure 1).

**Figure 1. f1:**
[figure not shown]
Components and flow of the PREFER study.

PREFER is registered at Clinicaltrials.gov as NCT05454839 (South Africa) and NCT05454852 (Zambia).

### Study sites

PREFER will be conducted at 18 healthcare facilities in South Africa and 12 in Zambia (
Table 1). Study sites represent the facilities participating in the SENTINEL study of the AMBIT Project
^
16
^. For SENTINEL, local study teams first identified provinces and districts that were accessible, had a high burden of HIV, utilized the national electronic medical record system, and jointly provided diversity in setting (rural, urban), facility size, and nongovernmental support partners. Within each district, SENTINEL then selected a set of facilities that represented the desired diversity and were large enough to provide the sample sizes required. These were chosen with engagement from the relevant Departments and Ministries of Health, including national and district government health officials with responsibility for the sites. Further information about SENTINEL and preliminary results can be found at
www.sites.bu.edu/ambit.

**Table 1. T1:** PREFER study sites.

Facility	Setting	ART patients as of August, 2021	Average ART initiates per month, 2021
**South Africa**			
*West Rand District (Gauteng Province)*			
Clinic	Urban	1,783	16
Clinic	Rural	1,803	17
Clinic	Urban	1,897	16
Clinic	Urban	2,116	37
Clinic	Rural	2,301	13
Clinic	Urban	2,959	30
*Ehlanzeni District (Mpumalanga Province)*			
Clinic	Urban	6,365	49
Clinic	Rural	3,553	24
Clinic	Rural	1,946	9
Clinic	Rural	3,001	28
Community Health Centre	Urban	5,234	105
Health Centre	Urban	5,523	43
*King Cetshwayo District (KZN Province)*			
Clinic	Rural	1,182	11
Clinic	Rural	1,509	11
Clinic	Rural	2,231	10
Clinic	Rural	3,361	23
Clinic	Rural	5,190	34
Clinic	Urban	7,934	34
**Zambia**			
*Lusaka Province*			
Urban Health Centre	Urban	2,370	21
Referral Rural Health Centre	Rural	4,060	35
Health Center	Peri-urban	3,754	23
First Level Hospital	Urban	10,794	131
First Level Hospital	Urban	13,386	121
First Level Hospital	Urban	6,954	45
*Central Province*			
District Hospital	Rural	3,397	16
Urban Clinic	Urban	6,805	48
Urban Health Centre	Urban	3,753	17
Urban Health Centre	Urban	2,855	21
Mission Hospital	Rural	2,397	17
District Hospital	Rural	4,326	18

### Study population, informed consent, and enrollment

We will sequentially recruit adult (≥18 years old) ART patients on treatment for ≤6 months who present at the study sites for ART initiation, routine care, or unscheduled HIV-related care and provide written informed consent. We will exclude anyone who is unable to communicate in any of the languages into which the survey has been translated, is unwilling to take the time required to complete the survey on the day of consent, or who, in the opinion of study staff, is physically, mentally, or emotionally unable to participate in the study. Eligibility will be determined through completion of a survey screening form, which will also allow us to compare the sex and age distribution of the population enrolled in the survey with those of the full potentially eligible population (Extended data - Supplementary file 1).

At the study sites, clinic staff will inform potentially eligible patients that they may be eligible to participate in a research study when the patient checks in at the reception desk (i.e. as they enter the facility and make their initial contact with facility staff). Patients will be recruited consecutively as they arrive at the facility, based on availability of study interviewers. We expect this process to generate a representative sample of patients over the course of each enrollment day, accurately reflecting the diversity of eligible potential participants.

Written informed consent will be sought from all eligible participants, covering the survey, medical record review, agreement to be contacted for later focus group participation, and agreement to blood sample testing for prior ARV exposure (Extended data - Supplementary file 2). Participants will be informed of the risks or discomforts that may come from study participation, their rights as participants, data security and confidentiality, and information to contact the study team if questions or concerns arise. The consent process and questionnaire will be administered in a confidential space by a trained research assistant in a private location at the clinic during the periods while patients are waiting in queues for facility services (consultations or medication pickups). Participants will be assured that they will not lose their places in the queue as a result of study participation. Patients who start the survey but do not have time to complete it before reaching the front of the queue will be asked to return to the research assistant after receiving services, in order to complete the survey. We anticipate that each interview will last 75 minutes, including the consent process. Participants will be offered light refreshments during the study and will be given a token valued at approximately US$10 to thank them for their time and participation.

### PREFER survey of client characteristics and preferences

The PREFER survey instrument aims to describe the characteristics, experiences, concerns, and preferences of clients initiating or re-initiating ART. It will be a structured questionnaire designed for primarily quantitative analysis but with some open-ended questions (Extended data - Supplementary file 3). Questions will build on previous work of the AMBIT Project and on the authors’ experience in studying retention in HIV care
^
1,
3,
17–
19
^. The questionnaire has eight substantive sections, addressing the respondent’s demographics and socio-economic status, HIV testing history, HIV treatment history, current HIV care and treatment experience, other healthcare, preferences for features of treatment delivery, expectations, and costs of seeking care. Questions are designed to elicit information about participants’ past experiences with the healthcare system and identify changes that would potentially improve their future experiences.

As PREFER is a descriptive study that aims to describe participants’ self-reported experiences and preferences, rather than comparing outcomes or testing a hypothesis, sample sizes were chosen to optimize the use of study resources and time availability. Using the expected number of eligible patients at each study site, the number of such patients who are expected to visit the sites during the data collection period, and an anticipated data collection period of 90 days in each country, the study protocols allow a maximum enrollment of 2,500 participants per country. We anticipate that actual enrollment will be somewhat less than this, with a minimum target of an average of 50 participants per study site, or 900 in South Africa and 600 in Zambia; we expect these sample sizes to be sufficient to generate sufficiently precise results to the survey’s quantitative questions.

### Medical record review for outcomes and resource utilization

Using identifiers collected as part of the structured questionnaire, we will also collect follow up data from routine medical records for the period from each participant’s initial data entry (first presentation for testing or care) to 12 months after study enrollment, with an additional round of medical record data collection up to 24 months after study enrollment in South Africa. The objective of this component of the study is to describe early treatment outcomes and, using data from the survey, identify associations between client characteristics and their outcomes, in order to better match early treatment interventions with client needs.

Medical record data will be drawn from Tier.Net in South Africa and Smartcare in Zambia, paper records and registers maintained at the study sites, and other databases, such as South Africa’s National Health Laboratory Services database, to ascertain whether patients are retained in care during the first 6 months on ART. We will collect data on HIV treatment history and current engagement, medications dispensed, laboratory tests performed, comorbidities, and other healthcare provided by the site and recorded in the EMR during the study period. We note that the EMRs in both countries are largely limited to HIV care; they may capture data on tuberculosis and other conditions but generally do not contain information about services provided by other departments within the clinics.

### Post-enrollment focus group discussions to explore clients’ concerns and preferences

Participants will be asked during the consent process for their agreement to be contacted by telephone or e-mail at any time during the 12 months following study enrollment and invited to participate in a FGD. Focus groups will address the concerns raised by survey participants to explore in-depth the challenges clients face in the early treatment period.

We anticipate inviting up to 300 participants to participate in FGDs of up to 10 participants in each of up to 30 groups, 15 per country. We will purposively select PREFER sites which have sufficient numbers of enrollees and represent a diversity of settings and purposively identify participants who have a record of missed visits or who have expressed concerns about their care in the quantitative survey. Patients will be contacted by telephone or email, depending on their preference stated at enrollment. Study staff conversant in English and the appropriate local language and trained in qualitative research methods and human subjects protection will conduct the FGDs.

Before commencing the FGD, all participants will be briefly screened for eligibility and study staff will proceed with the informed consent process. We will document informed consent with a signature or a thumb-print and capture basic demographic information for each participant to allow linkage to their survey results. FGD leaders, who will be trained study research assistants, will remind all participants that anything said during the discussion must remain private and should not be shared beyond the group. The FGDs will conducted in a private setting in the clinic or community.

To guide the discussion and probe for more in-depth responses, FGD leaders will use an FGD guide developed based on responses to the PREFER survey and focusing on specific issues or concerns that participants raise in the survey (Extended data - Supplementary file 4). Anticipated topics, which may vary by country, include HIV treatment experience, patient preferences for receiving HIV treatment, and patient expectations of HIV care. The FGD will be audio recorded and the leaders will also take notes during the interview. FGDs should take no longer than two hours.

Prior to starting the focus group discussions, participants will also be asked to participate in a brief discrete choice experiment (DCE) to rank their specific preferences for features of treatment delivery, such as visit frequency and medication refill duration and location, in the first six months of care. The DCE will provide a series of hypothetical scenarios for receiving ART, each of which contains a combination of attributes that emerge as important in the survey, which we expect to include location, waiting time, months of ART dispensed at a time, friendliness of providers, cost, and/or other attributes. The DCE instrument will include a maximum of 10 attributes with no more than three response levels each. Each participant will evaluate a maximum of nine choice sets—two scenarios with a different hypothetical combination of attributes—with one repeated to check for internal consistency (Extended data - Supplementary file 5). Participants will select their preferred option, then be asked if they would use that option if it were available. We expect the DCE to take approximately 15 minutes per participant and to be administered in a quiet, private space before the FGD commences. DCE results will be combined with FGD outcomes to develop a more nuanced description of clients’ needs and preferences.

### Biological sample collection at South African sites to estimate prior ART exposure

For a subsample of South African study participants who are enrolled on the day of ART initiation or re-initiation who self-report as ART-naïve or not having been on treatment for a least 90 days, a dried blood specimen (DBS) will be collected from PREFER survey participants at some study sites. The objective of this component of the study is to add to the evidence base about the proportion and characteristics of the large group of clients who have prior ART experience but do not reveal this to healthcare providers. As these clients have, by definition, previously faced barriers to ART retention, understanding more about them is essential to improving early treatment outcomes.

Sites were chosen based on willingness of providers to create the dried blood spots after obtaining venous blood sample for routine ART initiation blood tests. Blood is drawn routinely as part of the standard of care ART initiation process in South Africa. DBS specimens will be extracted from the routinely collected blood samples drawn by existing clinic staff (nurses or phlebotomists), who are trained in safe and sterile collection techniques. For the study, a sample of 50μml will be extracted from an existing EDTA vacutainer tube with a capillary tube and placed onto a Whatman Protein 903 filter paper. A minimum of 3 dried blood spots will be completed for each patient. Specimens will be allowed to air dry for 2 hours after being taken, or according to assay instructions. Specimens will be covered with glycine weighing paper after drying. Collected, dried specimens will be stored in a -4°C freezer and be shipped in 6-weekly batches via courier to the University of Cape Town Division of Pharmacology, PK Laboratory for analysis. Specimens will be batch-screened for the presence of tenofovir diphosphate.

Participants who meet the inclusion criteria for this subsample (initiating or re-initiating ART and self-reporting as ART-naïve or not having been on treatment for HIV for at least 90 days) will be consecutively enrolled up to a maximum of 200 participants from all participating study sites combined. Enrollment in this subsample will begin when the consumables required for DBS creation have been procured and staff have been trained on standard operating procedures for creating a DBS. Consent for biological sample collection is included in the overall survey consent form.

### Data management

A screening register will be kept by the study research assistants to record the consent process and keep track of those who do not consent, to allow us to determine if our sample is biased by patient characteristics due to differential consent. The screening register will not contain any individual identifiers. It will request age category, gender, and months on ART, as needed to determine survey eligibility only.

Patient survey responses will be entered live at the time of the interview into an electronic database on Survey CTO (Dobility 2023) using handheld tablets. If there are power failures, data will be entered onto paper study forms and then transcribed into a database at the local study office. Survey data will be converted to SAS, STATA, or R for final cleaning and data analysis. All analytic databases will be password protected with access restricted to the members of the study team. All survey respondents will be assigned a seven-digit, sequential identification number. The study ID number will be used to identify individual subjects in the study databases and to link survey response data to patient retention outcomes data and for all data analysis. Once data are linked, identifiers will be removed from the analysis file and all subjects will be assigned a random study ID, which will be used for all analysis.

FGD audio files will be transcribed verbatim, then transcribed and translated into English for analysis.

Data for this study will be accessible only by key study personnel. Study ID numbers will be used in place of names or identifying information to safeguard participants’ privacy. All physical consent forms, questionnaires, and notes will be stored in locked cabinets, with access restricted to study personnel. All data will be collected on encrypted devices and stored on secure drives, with access restricted to study personnel. A fully anonymized data set may be posted to a public data repository when the protocol has been closed, if required by the funder and journal. 

### Data analysis and dissemination

We will first create a descriptive summary of the demographic and clinical characteristics of participants enrolled in the study and responses to each question using frequencies and simple proportions for categorical variables and medians with interquartile ranges for continuous variables. We will then stratify these baseline survey responses by site characteristics, time on ART, self-reported naïve v non-naïve treatment status, and/or patient characteristics such as age and sex, as data allow. Data will not be pooled across countries, but differences in results by country will be noted and discussed.

Utilizing follow up data collected from patient medical records, we will conduct a crude analysis reporting simple proportions with 95% confidence intervals of patients disengaging from care, defined as missing a scheduled clinical or medication pickup visit during the first 6 months after treatment initiation by more than 28 days. Next, we will compare the proportions of patient disengaged from care by key variables including age, gender, clinical stage at ART initiation, site characteristics, time on ART, and naïve v non-naïve treatment status.

If enrollment numbers allow, the analysis will include a simple unadjusted comparison of outcome groups (retained or disengaged) with respect to baseline predictors of outcomes. Potential predictors include demographic and clinical variables and geographic and facility-level factors (urban vs rural setting, facility type). Using a log-linear regression model, we will next estimate crude risk ratios and crude risk differences and their corresponding 95% confidence intervals. If any important differences are observed, we will proceed with an adjusted model. Should crude stratification techniques reveal potential effect measure modification, these analyses will not be adjusted but rather reported as stratified output.

For the FGD output, we will conduct a content analysis of the qualitative data using the Framework Method
^
20
^. We will use a combination inductive-deductive approach wherein most codes will be identified
*a priori*, aligned with the FGD guide and literature, but the coding process will allow for additional codes to emerge to form a final analytical framework. Data will be charted, summarized, and quotations will be presented to illustrate key points when appropriate. Results will be presented stratified by country and urbanicity of sites.

To analyze the DCE survey data collected before the FGDs, we will estimate the impact of each attribute on a participant’s choice using a conditional logit model and a random effects probit model. The DCE results will be triangulated with the survey and FGD finding to complement PREFER overall conclusions about client preferences.

For the analysis of prior ART exposure, the presence of TDF above 0.02μg/ml in blood samples will be considered as positive for previous ART use in the previous 3 months or as advised by the laboratory. We will report the proportion of those who have evidence of usage of TDF and, where possible, use the quantified measure to estimate frequency of ART usage, in the preceding 90 days. If sample size allows, we will also identify client characteristics associated with prior ART exposure, using survey responses and medical records.

The study results will be disseminated in several ways. The primary audiences for the results of this study are the South African National Department of Health and Zambian Ministry of Health and their partners, who will use the findings to improve retention in care during the early treatment period. In addition, we will use the results to inform the design of one or more new models of service delivery, which we expect to implement and evaluate during a later stage of this project. Many of the findings will also likely be of broader interest in South Africa and other countries and will be made as widely available as possible, through journals, websites, and conferences. Only aggregated, stratified data will be presented; it will not be possible to identify any individual patients from any of the results that are presented.

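### The disengagement analysis names no allowance for facility, although each country rests on 18 or 12 sites and the listed predictors include site-level factors

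*Protocol article*

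**What the plan says.** The Study sites section states that "PREFER will be conducted at 18 healthcare facilities in South Africa and 12 in Zambia". The survey section sets a "minimum target of an average of 50 participants per study site, or 900 in South Africa and 600 in Zambia". The two countries are analysed separately.

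Under Data analysis and dissemination, the plan for the medical-record outcome is this: "we will conduct a crude analysis reporting simple proportions with 95% confidence intervals of patients disengaging from care". It then continues: "Using a log-linear regression model, we will next estimate crude risk ratios and crude risk differences and their corresponding 95% confidence intervals". The candidate predictors include "geographic and facility-level factors (urban vs rural setting, facility type". The predictor comparison depends on enrolment being large enough, and an adjusted model follows only if the crude results show notable differences.

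For these analyses the article names no facility term, no cluster-robust variance and no facility random effect. The Limitations section mentions the small number of sites, but only as a limit on generalizing to other districts and provinces.

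**The concern.** Clients at one facility share staff, queues, dispensing practice and record-keeping, so their outcomes may be correlated. A standard interval for a proportion, or the model-based interval from a log-linear regression, takes every client as a separate unit of information. If the described methods are run in that default form, the intervals are too short wherever such correlation exists.

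The effect is sharpest for setting and facility type. These do not vary within a site, so an urban/rural contrast in South Africa compares 8 facilities with 10, not several hundred clients with several hundred others.

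What is at stake is the use of the results. They are meant to guide health ministries and the design of new service models, and the crude comparison decides whether an adjusted model is fitted. A chance difference between a few facilities could be reported as an effect of setting or facility type.

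**Working it through.** **Inputs from the article**
- Sites: 18 and 12. Minimum enrolment: 50 × 18 = 900 and 50 × 12 = 600, which reproduces the stated targets.
- Setting, counted from Table 1: South Africa 8 urban and 10 rural; Zambia 7 urban, 1 peri-urban and 4 rural. Peri-urban is grouped with urban below.
- Facility type, counted from Table 1: South Africa has 16 clinics, one community health centre and one health centre. Zambia has seven labels over 12 sites, four of them used once (referral rural health centre, health center, urban clinic, mission hospital).
- Early attrition cited in the Introduction: 26% (and 35.6%), used as a guide for the disengagement proportion p.

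**Assumption.** The documents give no ICC for disengagement. The range 0 to 0.10 is assumed.

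**Formulas**
- Design effect: DEFF = 1 + (m − 1) × ICC, with m = 50 clients per site.
- Half-width of a 95% interval: 1.96 × √(p(1 − p)/N) × √DEFF.
- Actual coverage of an interval that ignores clustering: 2Φ(1.96/√DEFF) − 1.

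Ignoring clustering, at p = 0.26: 1.96 × √(0.26 × 0.74/900) = 2.9 points for South Africa, and 1.96 × √(0.26 × 0.74/600) = 3.5 points for Zambia.

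| ICC | DEFF | Half-width, N = 900 | Half-width, N = 600 | Coverage of unadjusted 95% interval |
|---|---|---|---|---|
| 0 | 1.00 | 2.9 | 3.5 | 95% |
| 0.01 | 1.49 | 3.5 | 4.3 | 89% |
| 0.02 | 1.98 | 4.0 | 4.9 | 84% |
| 0.05 | 3.45 | 5.3 | 6.5 | 71% |
| 0.10 | 5.90 | 7.0 | 8.5 | 58% |

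**False-positive rate for urban/rural.** Beta-binomial data were simulated (20,000 runs per setting) with no true difference, the Table 1 split of sites and 50 clients per site. A client-level Wald test of the log risk ratio at nominal 5% rejected in about 5% of runs at ICC 0, 11% at 0.01, 16–17% at 0.02, 29% at 0.05 and 42–43% at 0.10. A t-test on the facility proportions stayed at about 5% throughout.

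**Unequal sites.** If enrolment followed the 2021 initiation volumes in Table 1, the size-weighted mean cluster would be 80.1 (South Africa) and 91.0 (Zambia). Over ICC 0.01 to 0.10, DEFF would then be 1.79 to 8.91 and 1.90 to 10.0. The client-level urban/rural test would reject in 12–47% and 9–39% of runs, and the facility-level t-test in 4–7%. This is a scenario only, since recruitment depends on interviewer availability.

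**More clients do not cure it.** The article says that "the study protocols allow a maximum enrollment of 2,500 participants per country". That would be 2,500/18 = 139 and 2,500/12 = 208 clients per site, so even at ICC 0.01 DEFF would be 1 + 138 × 0.01 = 2.38 and 1 + 207 × 0.01 = 3.07.

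**Facility type needs no ICC.** Where a type has one site, its comparison with any other type is also a comparison of that one site with the rest. No client-level model can separate the two.

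**The case against.** The strongest defence is that independence is nowhere stated. The article names estimands and a model but no variance estimator; crude and simple can be read as unadjusted for covariates; and the variance method may sit in a full protocol or analysis plan that is not shown. This stands against saying that every interval in the study treats clients as independent. Intervals are named only for the disengagement analyses, and the point is conditional on a default analysis. It does not remove the point, because the article does fix the methods and does list site-level predictors, and those methods followed as written give intervals based on clients.

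The facilities were also chosen on purpose. If the target is only clients at these sites, facilities act as fixed strata and the interval for an overall proportion need not be too narrow. Client-level predictors such as age usually suffer less too. Both softenings stand, but neither helps a contrast of setting or facility type.

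The study is descriptive, its predictor analysis is conditional on enrolment, and no significance test is specified. So a reader who infers that facility-level predictors are bound to look significant goes too far: the false-positive rate rises, but it is not certain.

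Two further readings are tempting and not supported:
- That the statement "we expect these sample sizes to be sufficient to generate sufficiently precise results" rests on independence. It concerns the survey questions and no precision calculation lies behind it; the article says "rather than comparing outcomes or testing a hypothesis, sample sizes were chosen to optimize the use of study resources and time availability".
- That the discrete choice experiment ignores repeated choices by one person. A random effects probit is planned beside the conditional logit.

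**Conclusion.** The point holds in a bounded form. The described disengagement analysis makes no allowance for facility, with 18 or 12 sites per country and site-level factors among the predictors. If it is run on clients as independent units, DEFF at 50 per site is 1.49 to 5.90, coverage about 89% to 58%, and the urban/rural false-positive rate about 11% to 43%, for an assumed ICC of 0.01 to 0.10. These sizes rest on that assumption and are zero at ICC 0; the article does not establish that retention varies strongly by facility.

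The case is firmest for setting, where the facility is the unit of information, and for single-site facility types, where type and site are inseparable whatever the ICC. It is weaker for client-level predictors that vary within site, and for an overall proportion meant to describe these facilities only.

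**What to change.** In Data analysis and dissemination, state that the disengagement intervals, risk ratios and risk differences are computed with facility as the cluster and a correction for few clusters. Modified Poisson regression or GEE with a bias-corrected robust variance (for example Kauermann-Carroll or Fay-Graubard) would do, as would a facility random effect.

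Analyse urban/rural setting on facility-level degrees of freedom, for example by comparing facility proportions, which leaves 18 − 2 = 16 degrees of freedom in South Africa and 12 − 2 = 10 in Zambia. Report facility types represented by one site descriptively only, without a risk ratio or interval attributed to type.

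If the overall proportion is meant to describe only the study facilities, say so and treat sites as strata for that estimate.

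The cost is a few lines of code, some wording and wider intervals. No extra participants or data are needed.
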